Staffing combination (inner setting) is self-recorded by the AR2 providers. Due to varying AR2 staffing from shift to shift, we anticipate variability in dosage and fidelity by different crews, which will be unconfounded with encounter features, conditional on time and place. Our primary approach will be regression models, logistic regression for 0/1 outcomes and a proportional hazards model for time-to-event outcomes, in which our measures of dosage and fidelity are covariates. The power calculations for these analyses are identical to the Aim 1 power analysis for comparisons across time discontinuities. Rather than comparing across time periods, we will be comparing across high/low dose and high/low fidelity. Certain patients may be more receptive to AR2 services causing the AR2 to provide a greater dosage and maintain higher fidelity to the AR2 model. While we have no direct measure of “receptivity,” we will use a collection of patient features potentially correlated with receptivity including patient substance abuse profile, number of prior overdoses, age, race, and sex. We will use propensity score weighting to reweight high dosage patients so their features collectively resemble the features of low dose patients. Outcome models using these weights will estimate the treatment effect of receiving a low dose, answering what would happen to low dose patients if instead they were give a high dose of AR2 services. Similarly, we can reweight patients receiving high fidelity AR2 response to resemble low fidelity AR2 response, so that the outcome model estimates the effect of receiving low fidelity for those patients who actually received low fidelity AR2. Although dosage and fidelity are not 0/1 measures, we will consider dichotomizing them if high/low dosage and high/low fidelity have clear boundaries in practice.

- d. **Evaluating barriers and facilitators to AR2 implementation:** In order to supplement the approach to implementation analysis described above, we aim to add a qualitative approach to understanding and describing provider and process level individual perspectives that may influence implementation. This additional approach acknowledges that, while guided by theoretical implementation frameworks, a purely quantitative approach could miss important contextual aspects of implementation that

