- b. **Paired encounter analysis.** For the analysis of paired encounters (one AR2 and a non-AR2 occurring while the AR2 was on another call), we will use an exact McNemar's test for paired data for 0/1 outcomes (death, relapse) and a Cox proportional hazards model for paired data for censored time to event outcomes (time to treatment linkage, time to subsequent overdose). For each AR2 encounter we try to identify a non-AR2 encounter at the same time period within the AR2 response zone. If we find one, these pair of encounters are labeled as a pair and we will follow the patients for 60 days for linkage and non-fatal overdose, and 24 months for fatal overdose, and record outcomes. If multiple non-AR2 encounters happen simultaneously, then conditional logistic regression and stratified Cox models will extend the analysis from a 1-to-1 pairing to a 1-to-many matching. For our power calculations we assume a 1-to-1 pairing, a one-sided test for a reduction in adverse outcomes with  $\alpha = 0.05$  and a power level of at least 0.80. To detect a 50% reduction in the death rate attributable to the AR2 (assumed reduction from 10% to 5%), we need 370 pairs of encounters. To detect a 50% reduction in the rate of repeat non-fatal overdoses (from 30% to 15%), we need 105 pairs of encounters. To detect a 50% reduction in the hazard rate of time to subsequent overdose (equivalent to roughly 19% having a subsequent overdose within one year to 9.5%), we need 200 pairs of encounters. To detect an increase of 50% in the odds of seeking treatment within 60 days of an overdose (from 26% seeking drug treatment after an overdose within 60 days to 35% with AR2), we need 360 pairs of encounters.

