- c. **Comparisons across time discontinuities.** For outcomes underpowered with a paired analysis, we will compare AR2 encounters during AR2 operational hours (10AM-6PM) to non-AR2 encounters outside of AR2's operational hours (6PM-10AM) within the Kensington zip code. Since comparison encounters will not be occurring at the same times as the AR2 encounters, there is a risk of confounding. We will first assess whether AR2 and non-AR2 patients encountered differ on likely confounders (e.g. age, race, sex, substance use profile such as type of drug, injected or not). Ideally focusing exclusively on patient encounters closest to AR2 time boundaries (near 10AM and 6PM) will provide sufficient observations and minimize the risk of confounding. If we find no differences (e.g. patients overdosing earlier in the day resemble those who overdose later in the day) then we will analyze the data as a simple binomial test of proportions (for 0/1 outcomes) or estimate the hazard ratio (for time to event outcomes). If we do find differences, then we will propensity score reweight comparison cases on age, sex, race, and substance use profile so that they do match. The following power calculation assumes no propensity score reweighting, but if propensity score reweighting is needed, the effective sample size, computed as  $(\sum w_i)^2 / \sum w_i^2$  where  $w_i$  is the propensity score weight, will need to equal the needed sample size in the power analysis. This depends on how many comparison encounters closely resemble the AR2 patients. To detect a 50% reduction in the death rate

attributable to the AR2 (assumed reduction from 10% to 5%), we need 380 encounters in each arm. To detect a 50% reduction in the rate of repeat overdoses (from 30% to 15%), we need 105 encounters in each arm. To detect a 50% reduction in the hazard rate of time to subsequent overdose (equivalent to roughly 19% having a subsequent overdose within one year to 9.5%), we need 200 encounters in each arm. To detect an increase of 50% in the odds of seeking treatment within 60 days of an overdose we need 380 encounters in each arm.

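### The time-of-day comparison adjusts for confounders only if an undefined preliminary check finds differences, and its weighting list omits number of prior overdoses

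*Protocol*

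**What the plan says.** Protocol section 5.5, AIM 1 Analysis, item c (Comparisons across time discontinuities) covers outcomes for which the paired analysis lacks power. It sets AR2 encounters between 10AM and 6PM against non-AR2 encounters between 6PM and 10AM, and acknowledges that the different hours bring a risk of confounding. The rule has two branches:

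- The groups are first compared on likely confounders. Age, race, sex and substance use profile are given as examples, with no threshold or metric. If no differences are found, "then we will analyze the data as a simple binomial test of proportions (for 0/1 outcomes"; time-to-event outcomes get a hazard ratio, with no adjustment described.
- If differences are found, the plan is to "propensity score reweight comparison cases on age, sex, race, and substance use profile so that they do match". This list is not introduced as examples.

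The power calculation assumes no weighting. If weighting is needed, the effective sample size (Σw)²/Σw² must reach the stated size.

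Section 3.1, Aim 3, item c also plans propensity weighting, to make high-dose AR2 patients resemble low-dose ones. There the covariates are "patient substance abuse profile, number of prior overdoses, age, race, and sex", so prior overdoses are listed separately from substance use profile.

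**The concern.** The comparison is not randomised, and adjustment is the main protection inside this design. Making it depend on a preliminary look treats a finding of no difference as evidence of balance, which it is not at 105 to 380 per arm. An imbalance that escapes the check passes into an unadjusted test.

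Prior overdose is a plausible predictor of both repeat overdose and death, the outcomes being compared. It is missing from the weighting list, so neither branch targets it. Restricting the analysis to first encounters within the study period does not equalise overdose history before that period.

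At stake is a modest false benefit, or a masked one, attributed to AR2 on any outcome that falls to this design.

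**Working it through.** **The plan's own figures.** Item b (paired analysis) specifies "a one-sided test for a reduction in adverse outcomes" with alpha 0.05 "and a power level of at least 0.80". Item c does not restate this, but its sizes reproduce on that basis.

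- Death: "attributable to the AR2 (assumed reduction from 10% to 5%), we need 380 encounters in each arm". With p̄ = 0.075, n = (1.645√0.13875 + 0.842√0.1375)²/0.05² = 342.1, so 343. With the continuity correction, (n/4)(1 + √(1 + 4/(n×0.05)))² gives 382.
- Repeat overdose: "from 30% to 15%), we need 105 encounters in each arm". The same formulas give 95 uncorrected and 108 corrected.
- Time to overdose: "19% having a subsequent overdose within one year to 9.5%), we need 200 encounters in each arm". Freedman events = 2.487² × (1.5/0.5)² = 55.7, so 56; 56/(0.19 + 0.095) = 197.
- Treatment seeking at odds ratio 1.5 from 26%: 383 corrected, against 380 stated.

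Two-sided versions give 474, 134, 249 and 480 and do not fit. The sample sizes are not in dispute, and a one-sided 0.05 outcome test is the right basis for what follows.

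**Assumed inputs.** The protocol gives no confounder distribution and does not call the check a significance test. Assume one binary risk factor, 40% in comparison patients and 32% in AR2 patients; risk ratio 2 or 3 for the outcome; no AR2 effect; a comparator outcome of 30%; and a two-sided 0.05 balance test.

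**Chance that the check misses the imbalance.** This is approximately Φ((1.96·s0 − 0.08)/s1), with s0 = √(2×0.36×0.64/n) and s1 = √((0.40×0.60 + 0.32×0.68)/n).

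- n = 105: (1.96×0.0663 − 0.08)/0.0660 = 0.755, giving 77%
- n = 200: (1.96×0.0480 − 0.08)/0.0478 = 0.294, giving 61-62% (61% by simulation)
- n = 380: (1.96×0.0348 − 0.08)/0.0347 = −0.339, giving 37%

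**Spurious effect if unadjusted.**

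- Risk ratio 2: low-risk rate = 0.30/(0.6 + 0.8) = 0.2143; AR2 rate = 0.2143 × (0.68 + 0.64) = 0.2829, a false relative reduction of 5.7%.
- Risk ratio 3: 0.30/(0.6 + 1.2) = 0.1667; 0.1667 × (0.68 + 0.96) = 0.2733, a false reduction of 8.9%.

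**One-sided error of the rule** (simulation, 200,000 replicates, stratified adjustment when the check detects a difference; ranges cover risk ratio 2 to 3):

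| n per arm | Check misses | Two-branch rule | Always adjusted |
|---|---|---|---|
| 105 | 77% | 6.6-7.5% | 5.0-5.1% |
| 200 | 61% | 6.6-7.7% | 5.0-5.1% |
| 380 | 37% | 6.2-7.0% | 5.0-5.1% |

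With no true imbalance, the two-branch rule gives 4.7-4.8%. With the same 8 points reversed, it gives 2.9-4.0%.

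**Factor neither checked nor weighted.** Error ≈ Φ(d/SE − 1.645), where d is the spurious difference and SE = √(2p̄(1−p̄)/n).

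- n = 105: d/SE = 0.0171/0.0627 = 0.273 gives 8.5%; 0.0267/0.0624 = 0.427 gives 11%.
- n = 380, 30% base rate: 0.0171/0.0330 = 0.520 gives 13%; 0.0267/0.0328 = 0.813 gives 20%.
- n = 380, 10% base rate (the death outcome): risk ratio 3 gives d = 0.100 − 0.0911 = 0.0089, d/SE = 0.0089/0.0213 = 0.417, hence 11%; risk ratio 2 gives about 8%.

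The protocol itself pairs 105 with a 30% rate and 380 with a 10% rate for death. The 13-20% figures show what a larger sample does at a 30% rate.

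**The case against.** Several objections have force.

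- **The design is secondary.** Sections 3.1 and 5.5 prefer simultaneous paired encounters. Item c also hopes to concentrate on encounters near 10AM and 6PM, and item d offers a difference-in-difference analysis aimed at day/night differences. This limits the point's weight but does not remove it: the boundary restriction is only an aspiration and would make the check less sensitive, and difference-in-difference is described as the last resort.
- **The 0.05 balance test is assumed.** The protocol could mean standardised differences, and several covariates could each trigger weighting. That stands, and the detection rates are illustrative. But no criterion is given, and the unadjusted branch is fixed in the protocol itself.
- **The sizes are minimums.** The protocol expects 600-1000 engagements. At 600 per arm the miss rate in this example is 17%, although first-encounter and boundary limits would reduce the number usable.
- **Prior overdoses might be checked,** because the check list is given as examples. The weighting list is not.

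A reader might infer more than the documents support, in four ways.

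- *That choosing the analysis by a pre-test itself breaks the error rate, or makes the standard error wrong.* The check looks at covariates, not outcomes. With no imbalance the error is 4.7-4.8%, and with imbalance the check lowers the error compared with never adjusting (7.0% against 20% at 380 per arm, risk ratio 3).
- *That the error among passed checks is the error of the plan.* With a 12-point imbalance, 380 per arm and risk ratio 3, it is about 12% in that subset, but the check passes only about 6% of the time and the overall error is about 5.5%.
- *That the bias must favour AR2.* The direction is unknown.
- *That every needed covariate is already in hand.* Section 4.4 lists EMS fields without a prior-overdose count and states no history before May 2019.

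**Conclusion.** The point holds as a recommended correction to a secondary analysis. The defect is residual measured confounding: an imbalance that the check misses goes unadjusted, and prior overdoses are not targeted even when weighting is used.

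For a checked factor, the excess is small in the example: about 6-8% overall against 5%, and below 5% if the imbalance runs the other way. For a factor neither checked nor weighted, as may happen with prior overdoses, it is larger: about 8.5-11% at 105 per arm and 13-20% at 380 with a 30% base rate, or about 11% at 380 with a 10% base rate and risk ratio 3.

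All of these rest on an assumed prevalence, risk ratio and balance test. The protocol supplies none of them, so the actual size of the bias cannot be derived from it.

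**What to change.** In section 5.5, AIM 1, item c:

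- Drop the conditional rule. Always weight, or regression-adjust, comparison encounters on age, sex, race and substance use profile.
- Add number of prior overdoses, as far back as the EMS records allow. Confirm and state that look-back period first.
- Use robust standard errors, and judge balance by standardised differences after weighting.
- Keep the unadjusted binomial test and hazard ratio as sensitivity analyses.
- Compare the needed 380, 105, 200 and 380 per arm with the effective sample size from the formula already in the paragraph, since weighting would now always apply.

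The cost is mainly wording, plus confirming the overdose history with the data-holding department. The downside is some loss of effective sample size. Adjustment removes only measured confounding, so the difference-in-difference analysis keeps its purpose.

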## **AIM 2 Analysis:**

- a. **Analysis plan and power calculation.** We will analyze separately abandoned home remediation and vacant lot abatement, but both will have a similar analysis structure. We will use a conditional Poisson regression model of the form  $\log(E(\text{count})) = \beta_0 + \beta_1 \text{clean} + \beta_2 \text{post} + \beta_3 \text{clean} \times \text{post}$ , where clean is a 0/1 indicator of whether the location went through blight remediation and post is a 0/1 indicator of whether the time period measured is post-blight remediation in the treated location. The conditional Poisson model accounts for the matched pairs of location.  $\exp(\beta_3)$  is of

primary interest, a ratio of rate-ratios, contrasting the relative change in overdose rates in the treated area pre- versus post-remediation with the relative change in overdose rates in the comparison locations.

We anticipate at least 55 blight remediated locations with which we can pair with 55 un-remediated locations. The average buffer area will have 1.2 overdoses per month. Under such circumstances we will be able to detect reductions of 50% or more in overdose rates with power 0.80.

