2  
3 **PRINCIPAL INVESTIGATORS:** [name] MS, [name] MS

4 **PROTOCOL TITLE:** Studying the PhilAdelphia Resilience Project as a Response to Overdose  
5 (SPARROw)

6  
7 **1. INTRODUCTION AND PURPOSE:**

8  
9 **1.1. Objectives:** The objective of this proposal is to evaluate the effectiveness and  
10 implementation of two City of Philadelphia Resilience Project programs to reduce  
11 opioid overdose: (1) the Alternative Response 2 (AR2) that accompanies ambulances  
12 responding to overdoses and aims to deliver harm reduction and care linkage to people  
13 who refuse hospital transport, and (2) blight remediation of abandoned buildings and  
14 land. This application leverages a natural experiment within the Resilience Project  
15 implementation to evaluate its impact on overdose outcomes.

16  
17 We propose to address the following Specific Aims:

18  
19 **SA1: Determine the effectiveness of the Resilience Project AR2 on opioid overdose**  
20 **outcomes for EMS patients who refuse hospital transport after overdose.** Using a  
21 quasi-experimental design, we will compare the proximal overdose outcomes (rates and  
22 timing of treatment linkage) and distal overdose outcomes (non-fatal overdoses within  
23 60 days and overdose deaths within 24 months) for patients who receive AR2  
24 engagement compared to those who, due to timing or location restrictions, receive  
25 traditional EMS care alone.

26  
27 **SA2: Evaluate the impact of Resilience Project blight remediation activities on**  
28 **fatal and non-fatal opioid overdose.** Blight remediation activities vary across time and  
29 space in Kensington. We will use a difference-in-difference design to compare fatal and  
30 non-fatal overdoses in the 60 days before and after any given remediation effort  
31 compared to the same time period in two nearby locations that did not get remediated  
32 but had comparable pre-blight remediation overdose rates. We will select one control  
33 location from within Kensington and one just outside the Resilience Project geographic  
34 boundary.

35  
36 **SA3: Evaluate implementation of the Resilience Project by a) characterizing the**  
37 **fidelity of the AR2 intervention in Kensington, b) measuring factors that moderate**  
38 **AR2 fidelity, including blight, c) assessing barriers and facilitators to AR2**  
39 **implementation, and d) determining the costs for AR2 and blight remediation**  

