- d. **Comparator Group:** For each blight remediation activity, we will randomly select two comparator locations that are at least 0.25 miles away that were eligible for but did not receive blight remediation in the 30 days prior to the intervention activity. The first comparator location will be in the Kensington zip code (comparator 1), allowing for a comparison in the neighborhood in which all Resilience Project activities are taking place. This will also allow us to evaluate if blight remediation can be linked to an absolute decrease in overdose without simply pushing drug use and overdose to a different location. The second comparator location will be outside the Kensington neighborhood in one of the immediately adjacent zip codes (comparator 2). This comparator allows us to evaluate the impact of blight remediation activities in a location where no Resilience Project efforts are taking place in order to account for any co-linear associations that may be due to other resilience project interventions but are independent of blight remediation.

We will use the ArcGIS tool Similarity Search to randomly pick the two comparator locations with unremediated abandoned houses or vacant lots for each blight remediation intervention location. Using the tool, we will first find a block group either within Kensington (comparator 1) or immediately outside of Kensington (comparator 2) that has the same sociodemographic profile of the matched blight remediation area, but did not receive remediation. We will then determine the geographic center of each selected block group, which will serve as the point locations around which outcomes are measured.

**AIM 3: Evaluate implementation of the Resilience Project by a) characterizing the fidelity of the AR2 intervention in Kensington, b) measuring factors that moderate AR2 fidelity, including blight, c) assessing barriers and facilitators to AR2 implementation, and d) determining the costs for AR2 and blight remediation interventions.**

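### The Aim 2 conditional Poisson model allows only for the matched pair, so its intervals can be too narrow if overdoses cluster or areas are shared

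*Protocol*

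**What the plan says.** Protocol section 5.5, Aim 2 Analysis, commits to a likelihood: "We will use a conditional Poisson regression model of the form". The mean is log-linear, with terms for a remediated location (β1), the later period (β2) and their product (β3); exp(β3) is the quantity of interest. On dependence it says: "The conditional Poisson model accounts for the matched pairs of location". No dispersion term, robust variance or clustering is named.

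The power statement begins: "We anticipate at least 55 blight remediated locations with which we can pair with 55 un-remediated locations". It takes a mean of 1.2 events per buffer each month and concludes: "we will be able to detect reductions of 50% or more in overdose rates with power 0.80". It gives no window, alpha or sidedness.

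Three other places bear on the variance:
- Section 1.1 (SA2) sets the window: "non-fatal overdoses in the 60 days before and after any given remediation effort".
- Section 3.1, Aim 2 d, gives each remediation activity two comparators, at least 0.25 miles away and each in a block group of similar sociodemographic profile. It continues: "We will then determine the geographic center of each selected block group". Outcomes are measured around that point. Whether a block group may be used twice, or buffers may overlap, is not said.
- Section 5.5, Aim 1 b, plans on 30% repeat non-fatal overdose with 60-day follow-up, and also on roughly 19% with a subsequent overdose in a year.

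**The concern.** Conditioning on the pair removes the level that its two locations share. It does not change the Poisson variance within a location and period, and it does not link one pair to another. Two features of the design can upset those assumptions.

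1. **Repeat events.** The restriction to a patient's first encounter belongs to Aim 1 (section 2.3 and the Aim 1 analysis). Aim 2 counts overdoses, so one person can contribute several to the same buffer and window.
2. **Shared areas.** Treated sites in one block group have the same profile and can be matched to the same comparator point. Section 3.1, Aim 2 c, reports 95 houses already sealed in one neighborhood, so treated buffers may overlap and one overdose may be counted at several sites.

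At stake are the width of the interval for exp(β3), the false-positive rate of its test, and the 0.80 power. Section 6.8 also plans a halfway analysis of blight effects to be shared with the city, which would rest on the same variance.

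**Working it through.** **1. Reproduce the stated power.** Inputs from section 5.5: 55 pairs, 1.2 overdoses per buffer-month, rate ratio 0.5. Under pure Poisson variance, Var(β3) is the sum of 1/expected count over the four cells, and power = Φ(0.693/SE − z).
- One-month counts: 55 × 1.2 = 66, so the cells are 66, 33, 66, 66. Var = 3/66 + 1/33 = 0.0758, SE = 0.275. One-sided 0.05: Φ(2.518 − 1.645) = **0.809**. Two-sided: 0.712, or 0.804 with two comparators per site.
- 60-day counts: 132, 66, 132, 132. SE = 0.195. Power is 0.945 two-sided and 0.972 one-sided.

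The 0.80 therefore matches one-month counts with no extra variation.

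**2. Power with dispersion φ** (SE multiplied by √φ, 1:1 pairs)

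| φ | one month, one-sided | 60 days, two-sided |
|---|---|---|
| 1 | 0.809 | 0.945 |
| 1.2 | 0.74 | not needed |
| 1.46 | 0.67 | 0.84 |
| 1.86 | 0.58 | 0.74 |

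With 60-day windows, 0.80 survives φ up to 1.62 (two-sided).

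**3. Repeats.** Let r be the chance that an event is followed by one repeat in the same buffer, t its delay, and W = 60 days. A repeat in the same window adds variance to the pre/post contrast. A repeat that crosses the remediation date subtracts from it. This gives

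φ = 1 + [r/(1 + r)] × (2A − B)/W,

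where A is the mean of (W − t) when positive, and B is the mean number of days of index timing that put index and repeat on opposite sides of the date.
- All local (r = 0.30), delays even over 60 days: A = B = 30, factor 0.5, φ = 1 + 0.231 × 0.5 = 1.115.
- All local, exponential delay with mean 20 days: A = 41.0, B = 18.1, factor 1.07, φ = 1.246.
- Half local (r = 0.15): φ = 1.065 and 1.139.
- All local with no delay: factor 2, φ = 1.9/1.3 = 1.46.

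The rejection rate of a nominal two-sided 5% test is 2[1 − Φ(1.96/√φ)]:

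| assumption | formula | simulation |
|---|---|---|
| half local, even delays | 5.8% | 6.1% |
| half local, mean 20 days | 6.6% | 6.7% |
| all local, even delays | 6.3% | 6.7% |
| all local, mean 20 days | 7.9% | 8.0% |
| all in same place and window | 10.5% | 10.6% |

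The simulations used 55 pairs and 2.4 events per cell; the no-repeat baseline was about 5%. If each repeat can trigger another at the same rate, the ceiling is φ = 1.3/0.7 = 1.86, or 15%; with all local and mean delay 20 days that chain gave 9.8%. At the other end, 19% a year is 1 − 0.81^(60/365) = 3.4% per 60 days. Even if all of it were local and immediate, φ = 1 + 2 × 0.034/1.034 = 1.07, or about 5.8%.

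**4. Reused comparators.** For two sites sharing an area, with remediation dates d days apart, the pre/post contrasts correlate at 1 − d/40 for d up to 60. The correlation is 1 at d = 0, zero at 40 and −0.5 at 60, then returns to zero at 120. Its positive and negative areas cancel (+15 over 0-60, −15 over 60-120), so widely spread dates average out. Simulated ratio of true to model SE with 55 sites drawing on 20 comparators: 1.00 with dates over 24 months, 1.12 with six batch dates (7.8% rejection), 1.58 with one common date (21.7%).

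**The case against.** The strongest reply is that a variance option is ordinary SAP content, that no SAP is at hand, and that nothing in section 5.5 rules out a robust variance. The quoted sentence is also true for what it covers: conditioning does handle the pair, and stable differences between locations largely cancel in β3. Part of this stands, since a SAP may already settle the matter. But the protocol names a specific likelihood and attaches a power figure that matches that likelihood with no allowance for extra variation, so the point concerns what is stated and not only what is left out.

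A reader might go further and infer that the protocol's own figures show the error bars to be too small. They do not:
- The 30% is a person-level Aim 1 figure for patients who refuse transport. Nothing ties the repeats to one buffer, and the 19%-a-year figure is far lower.
- Section 3.1 permits comparator reuse by silence but does not state it, and 55 un-remediated locations can be read as distinct. No buffer radius is given, so overlap cannot be sized.
- A rejection rate near 25% can be produced, but only if treated and comparator areas are both collapsed to about 30 and share near-identical dates. Section 1.1 describes activities that vary over time and space.
- Rejection near 12% from a location-by-period coefficient of variation of 0.5 rests on a value with no source in the protocol.
- It would be wrong to say that the stated error level is exceeded, because none is stated for Aim 2.
- It would be wrong to say that the 0.80 fails: on 60-day counts it survives a dispersion of 1.46.

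**Conclusion.** The point holds as a risk of unknown size, not as a demonstrated error. The named model allows for the pair only. Local repeats, or shared areas on similar dates, would make its intervals for exp(β3) too narrow. Assuming 55 pairs, 2.4 events per 60-day cell and a 30% repeat rate that is half or fully local with delays over weeks, the false-positive rate is about 6-8% against a nominal two-sided 5%. It is about 10% at the extreme of one repeat per person in the same place and window, and close to 5% if the lower repeat figure applies. Comparator reuse matters only when the reused areas have nearly the same calendar windows.

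The power claim cannot be judged until its basis is stated. On the one-month reading there is no reserve (0.809, falling to 0.67 at dispersion 1.46). On the protocol's 60-day windows there is some (0.945, falling to 0.84).

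**What to change.** Keep the mean model and exp(β3). Then:
- Base intervals and tests on a sandwich variance clustered on the distinct area (block group). In simulation a pair-level sandwich restored 4.4-5.3% under overdispersion, but it did not correct for reused areas.
- Draw comparators without replacement where possible, and say what happens when this cannot be done.
- Merge treated sites whose buffers overlap and whose dates are similar into one site.
- Restate the power with its window, alpha, sidedness and an explicit dispersion allowance. Reconcile the one-month basis with the 60-day windows, and the 1:1 pairs with the two comparators per activity.

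The cost is a few sentences and one software option. Intervals become slightly wider, or barely change if there is no extra variation, and merging may reduce the number of sites.
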